# Ground glass opacity resection extent assessment trial **(GREAT)**: A study protocol of multi-institutional, prospective, open-label, randomized phase III trial of minimally invasive segmentectomy versus lobectomy for ground glass opacity (GGO)-containing early-stage invasive lung adenocarcinoma

**DOI:** 10.3389/fonc.2023.1052796

**Published:** 2023-01-19

**Keywords:** segmentectomy, lobectomy, ground glass opacity, early-stage invasive lung adenocarcinoma, minimally invasive surgery

## Abstract

**Background:**

With widely use of computed tomography (CT) screening, an increasing number of early-stage lung cancers appearing as ground glass opacity (GGO) have been detected. Therefore, attempts have been made to investigate the feasibility of segmentectomy instead of lobectomy for those patients with GGO. However, the two recently released phase III trials failed to distinguish between GGO-containing lesions from pure solid nodules in the inclusion criteria, and the surgical methods did not distinguish between minimally invasive surgery and open thoracotomy. In addition, total lesion size≤ 2cm was taken as the inclusion criterion, instead of the solid part size recommended in the eighth edition of Union for International Cancer Control/International Association for the Study of Lung Cancer/American Joint Committee on Cancer (UICC/IASLC/AJCC) staging system. Hence, this present trial aims to figure out whether minimally invasive segmentectomy shows superiority in perioperative outcomes and non-inferiority in oncological prognosis over minimally invasive lobectomy among patients with GGO-containing clinical stage T1a-T1b lung invasive adenocarcinoma (IADC).

**Methods/design:**

Sample sizes are 1024 patients, who will be randomized into minimally invasive segmentectomy and lobectomy groups . Patients will be collected from 19 hospitals in China. Patients with peripheral mixed ground glass opacity (mGGO) with 0.5cm<total lesion size ≤ 3cm and 0.5cm<solid component size ≤ 2cm in lung window on CT scan are enrolled. The primary endpoint is 5-year recurrence-free survival (RFS). The secondary endpoints are 5-year overall survival (OS), perioperative outcomes and pulmonary function preservation. Kaplan-Meier curves are plotted to compare the survival outcomes between the two arms. Subgroup analyses are also performed to investigate the benefit of segmentectomy among different clinical variables.

**Discussions:**

If the primary endpoint shows at least non-inferiority in 5-year RFS of segmentectomy to lobectomy, minimally invasive segmentectomy can be recommended as an alternative to minimally invasive lobectomy. If second endpoints show non-inferior 5-year OS along with better perioperative outcomes and/or better pulmonary function preservation of segmentectomy compared with lobectomy after the primary endpoint has reached, minimally invasive segmentectomy may become a preferred procedure for patients with GGO-containing clinical stage T1a-T1b IADCs.

**Trial registration:**

Chinese Clinical Trial Registry. Trial registration number: ChiCTR2000037065.

**Clinical trial registration:**

https://www.chictr.org.cn/, identifier ChiCTR2000037065.

## Introduction

Lobectomy has been recommended as the standard procedure for clinical stage I lung cancer less than 3cm since the Lung Cancer Study Group (LCSG) trial was published in 1995. Sublobar resections including anatomical segmentectomy were reserved as a palliative procedure for high-risk patients who were functionally unfit for standard lobectomy (1). Nowadays, the scenarios of both thoracic surgery and disease profile have changed dramatically. The results of the LCSG trial performed nearly three decades ago may not be suitable to guide current practice.

First, the LCSG trial did not separate anatomical segmentectomy from wedge resection when comparing sublobar resections with lobectomy. In a propensity score matching analysis, anatomical segmentectomy showed 20-30% survival benefit than wedge resection in patients with stage I non-small cell lung cancer (NSCLC) (2), indicating that the oncological efficacy of anatomical segmentectomy may be different from wedge resection.

Second, the disease profile of lung cancers is quite different from 30 years ago. With the widespread use of computed tomography (CT) screening (3), small-sized pulmonary nodules, especially those containing ground glass opacity (GGO) component, are increasingly detected. Different from pure solid pulmonary nodules, the GGO component of a subsolid nodule is corresponding to non-invasive histology, while the solid component is considered as the invasive part of the lesion (4). In consequence, anatomical segmentectomy is reconsidered as an intentional procedure for selected patients with peripheral nodule ≤ 2cm, including adenocarcinoma *in situ* or nodule≥50% GGO appearance on CT scan or with a long doubling time under radiologic surveillance (≥400 days) according to the The National Comprehensive Cancer Network (NCCN) guidelines (5). Accordingly, current indications of segmentectomy as an intentional procedure cover only carcinoma *in situ* (Tis), microinvasive adenocarcinoma (T1mi) and some of T1a lesions (GGO-containing lesions sized ≤2cm with GGO component >50% and solid component <1cm). Our previous study has found that segmentectomy showed similar oncological results to lobectomy for both T1a and T1b GGO-containing lung adenocarcinomas, as long as the total lesion size was ≤3cm and the solid component size was ≤2cm (6). Thus, further randomized controlled study is warranted to see whether segmentectomy shows oncological non-inferiority to lobectomy in patients with GGO-containing clinical stage T1a and T1b invasive lung adenocarcinoma.

Third, thoracic surgery has come into the era of minimally invasive surgery (MIS) including video-assisted thoracic surgery (VATS) and robotic-assisted thoracic surgery (RATS). Compared with open lobectomy, VATS lobectomy demonstrates a better recovery of physical function according to the VIOLET study (7). Besides, MIS presents less postoperative pain and better quality of life after surgery, due to the rapid development of surgical skills and minimally invasive technologies (8, 9). More importantly, long-term oncological outcomes of MIS procedure are at least not inferior to open thoracotomy for early-stage lung cancers (10, 11). Now, MIS is the preferred approach according to the guidelines.

For now, new evidences are in need to see if minimally invasive segmentectomy is at least oncologically non-inferior to lobectomy in patients with clinical stage T1a and T1b GGO-containing IADCs. Also, it is important to answer whether MIS segmentectomy is indeed superior in improving perioperative outcomes and pulmonary function preservation. For these reasons, we are performing a multi-institutional, prospective, open-label, randomized phase III trial comparing the results of minimally invasive segmentectomy versus lobectomy in patients with GGO-containing clinical stage T1a-T1b invasive lung adenocarcinoma. The main purpose of this article is to introduce the study protocol of this clinical trial.

## Patients and methods

### Study setting and objectives

This study is a prospective, multi-institutional, open-label, randomized controlled phase III clinical trial in patients with clinical stage T1a-T1b lung adenocarcinoma with GGO component under the eighth edition tumor, node, metastasis (TNM) classification. The aims of the study are to investigate whether minimally invasive segmentectomy is non-inferior in oncological outcomes, but is superior in preserving pulmonary function and/or reducing perioperative risks, against minimally invasive lobectomy. This multi-institutional clinical trial is undertaken by Shanghai Chest Hospital, together with Zhongshan Hospital of Fudan University, Huashan Hospital of Fudan University, the First Affiliated Hospital of Zhejiang University School of Medicine, the Second Affiliated Hospital of Zhejiang University School of Medicine, Jiangsu Province People’s Hospital of Nanjing Medical University, Fujian Medical University Union Hospital, Fujian Medical University Cancer Hospital, Peking Union Medical College Hospital, Sixth Medical Center of Chinese People’s Liberation Army General Hospital, Sir Run Run Shaw Hospital, Liaoning Cancer Hospital & Institute, Union Hospital of Tongji Medical College, the Fourth Hospital of Hebei Medical University, the First Affiliated Hospital of Chongqing Medical University, the Affiliated Cancer Hospital of Zhengzhou University, the First Affiliated Hospital of Anhui Medical University, Nanjing Drum Tower Hospital, Beijing Chaoyang Hospital, Capital Medical University.

This study has been approved by the Institutional Review Board of Shanghai Chest Hospital (IRB approval date: January 19, 2021 and approve number: IS2112) and other participant hospitals. This clinical trial has been registered at Chinese Clinical Trial Registry (ChiCTR) (Registration number: **ChiCTR2000037065**).

### Inclusion criteria

Patients will be eligible if they fulfill all the following inclusion criteria. (1) Patient age is between 20 and 80 years old; (2) The location of the primary lesion should be in the peripheral 1/3 pulmonary field, where both lobectomy and segmentectomy with satisfactory proximal margin can be achieved; (3) Segmentectomy includes combined segmentectomy, but the extent of segmentectomy should be <1/2 of the corresponding lobe; (4) The primary lesion should appear as GGO containing on thin-sliced CT scan. Maximum size of the lesion should >0.5cm and ≤3cm, with the solid component size >0.5cm but ≤2cm on lung window (corresponding to cT1a-b); (5) Patients with ipsilateral multiple nodules can be included only if there are no more than 2 additional GGOs in a different lobe from the primary lesion, and must be peripherally located that can be removed by wedge resection. If the secondary lesion is a pure GGO, the size should be <1cm. If the secondary lesion is a mixed GGO, the solid component size should be <0.5cm. At most two wedge resections are allowed during the simultaneous operation for the primary lesion; (6) Patients with contralateral lesions can also be included if there are ≤3 GGO-containing lesions, with a solid component size smaller than that in the primary lesion; (7) All patients should be functionally fit for standard lobectomy and segmentectomy, with an American Society of Anesthesiologists (ASA) score of I-III and spirometry results of FEV1 ≥1.2L, FEV1% ≥60%, DLCO% ≥60%;(8) All patients are voluntary to participate in this clinical trial and written informed consents should be signed (**Table 1**).

**Table 1 T1:** Patient inclusion and exclusion criteria.

Inclusion criteria
1. Age between 20 and 80 years old;
2. Lesion locates in the peripheral 1/3 pulmonary field, and both lobectomy and segmentectomy (satisfied margin) can be done;
3. Segmentectomy includes combined segmentectomy, but the extent of segmentectomy should <1/2 of the lobe;
4. The primary lesion should appear as GGO containing on thin-sliced CT scan. Maximum size of the lesion should >0.5cm and ≤3cm, with the solid component size >0.5cm but ≤2cm on lung window;
5. Patients with ipsilateral multiple nodules can be included only if there are no more than 2 additional GGOs in a different lobe from the primary lesion, and must be peripherally located that can be removed by wedge resection. If the secondary lesion is a pure GGO, the size should be <1cm. If the secondary lesion is a mixed GGO, the solid component size should be <0.5cm. At most two wedge resections are allowed during the simultaneous operation for the primary lesion;
6. Patients with contralateral lesions can also be included if there are ≤3 GGO-containing lesions, with a solid component size smaller than that in the primary lesion;
7. All patients should be functionally fit for standard lobectomy and segmentectomy, with ASA score of I-III and spirometry results of FEV1 ≥1.2L, FEV1% ≥60%, DLCO% ≥60%;
8. All patients are voluntary to participate in this clinical trial and written informed consents should be signed;
Exclusion criteria
1. The primary lesion is in the right middle lobe; 2. Lesions requiring resection of more than 1/2 of the corresponding lobe, such as a basal segmentectomy and left upper lobe tri-segmentectomy;
3. Previous diagnosed malignancy within 5 years;
4. Unstable angina pectoris or myocardial infarction history within 6 months;
5. Stroke within 6 months; 6. Previous history of ipsilateral thoracic surgery.
Patient withdrawal
1. Benign lesions or AAH, AIS, non-adenocarcinoma cancer confirmed by intraoperative frozen section or postoperative final pathology;
2. Hilar or mediastinal lymph node metastasis confirmed by intraoperative frozen section;
3. Change of resection extent after randomization;
4. Patient requires to withdrawal or terminate the study for personal reasons.

GGO, ground glass opacity; FEV1, the forced expiratory volume in one second; DLCO, diffusing capacity of the lung for carbon monoxide; ASA, American Society of Anesthesiologists; AAH, atypical adenomatous hyperplasia; AIS, adenocarcinoma in situ.

### Exclusion criteria

Patients will be excluded if any of the following exclusion criteria is met. (1) The primary lesion is in the right middle lobe; (2) Lesions requiring resection of more than 1/2 of the corresponding lobe, such as a basal segmentectomy and left upper lobe tri-segmentectomy, to guarantee resection margin; (3) Previous diagnosed malignancy within 5 years; (4) Unstable angina pectoris or myocardial infarction history within 6 months; (5) Stroke within 6 months; (6) Previous history of ipsilateral thoracic surgery (**Table 1**).

### Patient withdrawal

Apart from inclusion and exclusion criteria mentioned above, those candidates will also be re-evaluated if any of the following exclusion criteria is appeared during the entire study. (1) Benign lesions or atypical adenomatous hyperplasia (AAH), adenocarcinoma *in situ* (AIS), non-adenocarcinoma cancer is confirmed by intraoperative frozen section or postoperative final pathology; (2) Hilar or mediastinal lymph node metastasis is confirmed by intraoperative frozen section; (3) Change of resection extent after randomization; (4) Patient requires to withdrawal or terminate the study for personal reasons (**Table 1**).

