### Surgery

Minimally invasive thoracic surgery including both VATS and RATS is required for this trial, including single-port, two-port, three-port or four-port incisions without rib spreading. Lobectomy and segmentectomy should be anatomically resected. The hilar structures should be separated and pulmonary vessels and bronchus should be divided respectively. Lobar fissure and intersegmental plane should be managed either by stapler alone or by stapler together with energy devices. Both segmentectomy and lobectomy groups should receive systemic lymph node dissection or sampling according to the NCCN guidelines (5).

Intraoperative frozen pathology is required for the resected specimen, including the pulmonary surgical margin of segmentectomy. If the segmental resection margin is positive of malignancy on frozen section, segmentectomy should be converted to lobectomy. All the intraoperative data including intraoperative complications will be carefully recorded. In addition, preoperative imaging, peripheral blood sample and intraoperative tumor specimen of each patient will also be collected for further exploratory research (**Figure 1**).

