### Pathological evaluation

Pathological examinations include intraoperative fast frozen evaluation and postoperative final pathology examination. For frozen section, the resected specimen, the margin of resected bronchus and the pulmonary surgical margin of segmentectomy will be assessed during surgical operations by an experienced pathologist. Specially, for the pulmonary surgical margin of segmentectomy, the shortest distance between the tumor and the pulmonary surgical margin should be measured. In the final pathology, routine examinations should at least include number of tumors, tumor location, tumor size, pathological types and subtypes, status of pleural invasion (PI), status of lymphovascular invasion (LVI), status of spread through air spaces (STAS), numbers of resected lymph nodes and lymph node stations. Histological subtypes and subtype percentage of invasive adenocarcinoma should be all presented according to the World Health Organization (WHO) classification of lung tumors (12, 13). Gene mutations test by next-generation sequencing is encouraged for each participant.

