Apart from the differences in inclusion criteria, the surgery approach and resection extent are different in this designed trial. No surgical approach was specified in either CALGB 140503 and JCOG 0802, which means that minimally invasive and open surgery can all be used (15, 16). Thoracic surgery has come into the era of minimally invasive surgery, which helps to reduce surgical trauma and function loss compared with traditional open thoracotomy. So, in this trial, the surgical approach is limited to minimally invasive surgery. The extent of pulmonary resection has now become the dominant factor on surgical risks and functional recovery. Unlike the sublobar group of CALGB 140503, which did not distinguish between wedge resection and segmentectomy, patients in JCOG 0802 were only divided into segmentectomy group and lobectomy group. While in JCOG 0802, there was no restriction on number of segments resected in the segmentectomy group. Segmentectomy in the GREAT study must be less than 1/2 of the corresponding lobe. If the number of segments removed ≥1/2 of the total segments of corresponding lobe, the patients will be withdrawn from the study.

Theoretically, when less lung tissue is removed, more lung function may be retained. However, pulmonary function preservation has failed to reach the expected level of 10% in the JCOG 0802 trial (16). From our previous study, if the number of segments removed ≥1/2 of the total segments of corresponding lobe, then the lung function loss of segmentectomy is similar to that of lobectomy (18). And in this previous observational study, VATS segmentectomy could reserve about 4-5% more FEV1 than corresponding VATS lobectomy. So, in the GREAT trial, segmentectomy is expected to have 5% less FEV1 loss than lobectomy.

Only with such evidences can early-stage lung cancer patients truly benefit from the advent of modern surgical techniques.

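### A frozen-section call alone meets a post-randomisation withdrawal criterion even if final pathology shows invasive adenocarcinoma, and the article does not reconcile what withdrawal means for follow-up and analysis

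*Protocol article*

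**What the plan says.** Under Patient withdrawal, item 1 of the protocol article covers benign lesions, atypical adenomatous hyperplasia (AAH), adenocarcinoma in situ (AIS) and other cancers, and applies when "non-adenocarcinoma cancer is confirmed by intraoperative frozen section or postoperative final pathology". Table 1 gives the same either/or rule: "Benign lesions or AAH, AIS, non-adenocarcinoma cancer confirmed by intraoperative frozen section or postoperative final pathology".

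Both readings are planned. Surgery states: "Intraoperative frozen pathology is required for the resected specimen, including the pulmonary surgical margin of segmentectomy". Pathological evaluation states: "Pathological examinations include intraoperative fast frozen evaluation and postoperative final pathology examination". Under Randomization, allocation takes place the day before the operation, so every frozen reading comes after it.

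The consequence of meeting a criterion is described in several ways:

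- The section heading and Table 1 call it patient withdrawal.
- The sentence that introduces the list says "those candidates will also be re-evaluated if any of the following exclusion criteria is appeared during the entire study".
- The Discussion says of a different rule, the limit on resection extent, that "the patients will be withdrawn from the study".
- Follow-up is prescribed for each qualified patient after resection, and the term is not defined.
- Statistical analysis promises ITT for all enrolled patients, and PP for those who completed the trial in compliance with the protocol.

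**The concern.** Frozen section is provisional and final pathology is definitive. A rule that either one can trigger lets the provisional reading decide against the definitive one. A patient called AIS in theatre and invasive adenocarcinoma in the final report belongs to the population the trial asks about, yet meets a withdrawal criterion. Because this happens after randomisation, the loss is not a screening failure. It removes part of a randomised comparison.

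Second, the article does not settle what happens to such a patient. ITT of all enrolled patients requires their outcomes, and nothing states that follow-up continues after a histology withdrawal. Sites could read the passages differently. Blood loss, operation time, drain duration, length of stay, morbidity and 6-month FEV1 describe the operation performed, and the patient was selected for it on CT before histology was known. Dropping those data would have no scientific reason behind it, and the Conclusions rest the preferred-procedure claim partly on these endpoints.

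**Working it through.** **1. The rule when the two readings disagree**

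| Frozen section | Final pathology | Criterion met as written | Target population |
|---|---|---|---|
| invasive adenocarcinoma | invasive adenocarcinoma | no | yes |
| invasive adenocarcinoma | benign, AAH, AIS or other cancer | yes | no |
| benign, AAH, AIS or other cancer | benign, AAH, AIS or other cancer | yes | no |
| benign, AAH, AIS or other cancer | invasive adenocarcinoma | **yes** | **yes** |

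Only the last row gives a wrong result. It disappears if final pathology governs.

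**2. The plan's own sample size**

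Inputs from Sample size calculation: 5-year recurrence-free survival (RFS) 91%, margin 5 points, one-sided alpha 5%, power at least 80%, drop-out 5%, total 1024. The formula is not named. A Schoenfeld calculation comes close:

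- Hazard ratio at the margin: ln(0.86)/ln(0.91) = 1.599, with logarithm 0.4695.
- Events: 4 × (1.645 + 0.842)² / 0.4695² = 112.2.
- Mean event probability: (0.09 + 0.14)/2 = 0.115, so 112.2/0.115 = 975.5 patients.
- With drop-out: 975.5 × 1.05 = 1024.3, or 975.5/0.95 = 1027.

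**3. How many patients (assumed rates)**

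The documents give no frozen or discordance rate. Assume that 5–10% of patients receive an ineligible frozen call and that 10–30% of those calls are overturned:

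- Target patients wrongly meeting the criterion: 1024 × 0.05 × 0.10 = 5, up to 1024 × 0.10 × 0.30 = 31 (0.5–3% of the total).
- All patients with such a call: 1024 × 0.05 = 51, up to 1024 × 0.10 = 102.
- The 5% drop-out allowance is also 51 patients.

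**4. Power, if these patients leave the analysis**

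Power = Φ(√(events/4) × 0.4695 − 1.645), with events = 0.115 × N:

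| Loss | N | Power |
|---|---|---|
| none | 1024 | 0.817 |
| 5% drop-out only | 973 | 0.799 |
| 5% drop-out, then 0.5% | 968 | 0.797 |
| 5% drop-out, then 3% | 944 | 0.788 |
| 5% drop-out, then 10% | 876 | 0.761 |

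On a difference-of-proportions basis at 91%, power after 5% drop-out and a further 10% loss is still 0.826. The shortfall therefore depends on the formula.

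**5. Bias, if losses differ by arm**

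If a fraction f with RFS r is removed, the RFS of those who remain is (0.91 − f·r)/(1 − f). Assume r = 0.98 to 1.00.

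- Equal f in both arms: shift 0.
- f = 0.5% against 3%: 90.96% − 90.78% = 0.18 points (r = 0.98); 90.95% − 90.72% = 0.23 points (r = 1.00).
- f = 5% against 10%: 90.63% − 90.22% = 0.41 points (r = 0.98); 90.53% − 90.00% = 0.53 points (r = 1.00).

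The margin is 5 points. The arm that loses more low-risk patients looks worse.

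**The case against.** The strongest reply is that the article never says such patients are lost. Its operative sentence speaks of re-evaluation, which could mean waiting for the final report, and ITT is promised for all enrolled patients. The phrase about withdrawal from the study concerns resection extent, and a qualified patient may simply be an eligible one. This stands: loss of outcomes is a possibility, not a stated consequence. It does not remove the point, because the heading and Table 1 say withdrawal without qualification and no passage says follow-up continues.

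A reader might also infer that the frozen call is made with knowledge of the arm, since "the margin of resected bronchus and the pulmonary surgical margin of segmentectomy will be assessed during surgical operations by an experienced pathologist" and the trial is open-label. The article says nothing either way about masking the pathologist, and gives no reason why the arm would change a benign or AIS call. Final pathology examines the same lobar or segmental specimen with no stated masking, so the inference would apply there equally. It does not support the fix and is not relied on.

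It is also tempting to leave histologically ineligible patients out of the RFS and overall survival (OS) analyses. That would be a post-randomisation exclusion against the ITT promise, and it ignores that the operation is chosen on CT before histology is known.

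Finally, an article condenses a fuller protocol, which may settle precedence and follow-up. That is fair for details left out. The either/or rule, however, is stated twice, so it is a rule as written and not an omission. Eligibility also requires a solid component above 0.5 cm, which the Introduction treats as the invasive part, so ineligible frozen calls may be few.

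**Conclusion.** The point holds in a limited form. As written, a provisional frozen reading alone meets a post-randomisation withdrawal criterion, including for patients whose final pathology places them in the target population. The passages on withdrawal, re-evaluation, follow-up and ITT are not reconciled.

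Whether outcomes are lost depends on whether withdrawal ends follow-up or removes patients from ITT, and the article does not say that it does. A patient withdrawn on an overturned frozen call would in any case leave the PP set, because that patient has not completed the trial in compliance, and PP carries weight in a non-inferiority comparison.

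The true size is unknown. The 5–31 and 51–102 patients, the power losses and the shifts of about 0.2 to 0.5 points all rest on assumed rates, and the power and bias figures further assume that the patients leave the analysis. Within those assumptions the effect on the primary result is small. The reason to act is that the rule gives a wrong result in a foreseeable case and is cheap to correct.

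**What to change.** Amend Patient withdrawal item 1, Table 1, Follow-up and Statistical analysis so that they agree, and state that, for trial data and analysis:

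1. Final pathology alone defines histological ineligibility.
2. That definition is used only for the PP set or a sensitivity set.
3. All randomised patients stay in follow-up and in the ITT analyses of RFS, OS, perioperative outcomes and FEV1, whatever the frozen or final histology.

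How the operation responds to a frozen result is a clinical matter and is left unchanged.

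Keeping ineligible patients in ITT has one price. If a share w of patients has no events in either arm, a true 5-point deficit among the rest appears as 5 × (1 − w), for example 4.5 points at w = 10%. The set defined by final pathology shows how far this matters.

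The cost is amendment wording and continued routine follow-up, including 6-month spirometry, for a few more patients. No new procedure is needed, because final pathology is already part of the examination.

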### Follow-up

Each qualified patient after surgical resection should take postoperative follow-up in out-patient department. Within the first month after operation, patient will receive chest X-ray examination to assess the extent of residual lung expansion after radical resection. Pulmonary function examination *via* spirometry test will be performed in each participant at 6 months after surgery. In the first three years after surgery, patients need to receive chest CT scanning, neck and abdomen ultrasound examination and serum tumor markers every six months. Thereafter, the above examinations need to be repeated once a year until the fifth year after operation. All follow-up information is carefully recorded.

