### Statistical analysis

A two-sided *p*<0.05 is set as a statistical difference. Pearson χ^2^ or Fisher’s exact test and Student t test are performed for the comparison of baseline characteristics, perioperative outcomes and the pulmonary functions. Comparisons of OS and RFS between minimally invasive segmentectomy and lobectomy groups are all estimated by Kaplan-Meier method and testified by the two-side Log-rank test. Cox proportional hazard regression model will be used to evaluate the hazard ratio of minimally invasive segmentectomy group and minimally invasive lobectomy group for OS and RFS, respectively. Subgroup analyses will also be performed by total lesion size ≤ 2cm or 2cm-≤3cm. Intention to treat analysis (ITT) will be performed for all enrolled patients. Per protocol analysis (PP) will be performed for patients who have completed the trial in compliance with the protocol.

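### Withdrawing patients whose resection extent changes after randomisation conflicts with the promised ITT analysis, and the named triggers arise only in the segmentectomy arm

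*Protocol article*

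**What the plan says.** Patients are randomised the day before surgery (Randomization), so any change made in the operating room comes after allocation. Five places in the protocol article then bear on what happens to such a patient.

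- **Patient withdrawal, item 3, and Table 1:** "Change of resection extent after randomization" is a listed reason, with no exception for a change that the protocol itself orders. The sentence introducing the list is softer than its heading: "those candidates will also be re-evaluated if any of the following exclusion criteria is appeared during the entire study".
- **Surgery:** "If the segmental resection margin is positive of malignancy on frozen section, segmentectomy should be converted to lobectomy".
- **Discussion:** "If the number of segments removed ≥1/2 of the total segments of corresponding lobe, the patients will be withdrawn from the study".
- **Follow-up:** "Each qualified patient after surgical resection should take postoperative follow-up in out-patient department". The same section schedules spirometry at 6 months for every participant.
- **Statistical analysis:** "Intention to treat analysis (ITT) will be performed for all enrolled patients", and "Per protocol analysis (PP) will be performed for patients who have completed the trial in compliance with the protocol". Neither analysis is named as primary, and nothing says how a withdrawn patient enters either one.

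**The concern.** A surgeon who follows the Surgery section after a positive segmental margin thereby triggers a listed reason for withdrawal. The conversion is a foreseeable result of being assigned segmentectomy, so it belongs to the strategy that the trial is meant to evaluate. The half-lobe rule in the Discussion works the same way, because it is judged on the segments actually removed. A patient with the same tumour in the lobectomy arm meets neither trigger and stays in.

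If withdrawal means no further follow-up, or no place in the analysis, segmentectomy is represented mainly by the patients in whom it went as planned, and the protection of randomisation is lost. In a non-inferiority trial, a shift in that direction makes a false conclusion of non-inferiority more likely. An analysis plan written later cannot recover RFS or 6-month FEV1 data that were never collected.

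**Working it through.** **The plan's own figure.** Inputs from Sample size calculation: 5-year RFS 91%, margin 5 points, one-sided alpha 5%, power 80%, drop-out 5%, total 1024. The article names no formula. A Schoenfeld calculation comes close:

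- Hazard ratio at the margin: ln(0.86)/ln(0.91) = 1.599.
- Events: 4 × (1.645 + 0.842)² / (ln 1.599)² = 112.2, so 113.
- Patients: 113 / 0.115 = 983, where 0.115 is the mean of 9% and 14%.
- With drop-out: 983 / 0.95 = 1035, which is 1.1% above 1024.

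The sample size is not in dispute. It supplies only the evaluable number per arm: 512 × 0.95 = 486.

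**The passages side by side**

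| Event | Arm in which it can occur | Status in the article | ITT sentence |
|---|---|---|---|
| Positive segmental margin, converted to lobectomy | Segmentectomy only | Falls under withdrawal item 3 | Counts as enrolled |
| Segmentectomy reaching half the lobe or more | Segmentectomy only | Withdrawn (Discussion) | Counts as enrolled |
| Any other change of extent | Either | Falls under withdrawal item 3 | Counts as enrolled |

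The last two columns are compatible only if withdrawn patients are still followed and analysed as randomised. The article does not say so.

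**Effect on RFS if these patients are lost.** The documents give no conversion rate and no RFS for converted patients, so both are assumptions. Let c be the share of the segmentectomy arm withdrawn (2-6%) and r its 5-year RFS (60-80%). True RFS is 91% for lobectomy and 86% for segmentectomy, exactly at the margin. Nobody leaves the lobectomy arm under this rule.

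- Visible segmentectomy RFS: p = (0.86 − c·r)/(1 − c).
- Visible difference: d = 0.91 − p.
- SE = √[0.91 × 0.09/486 + p(1 − p)/(486(1 − c))].
- Chance of declaring non-inferiority: Φ((0.05 − d)/SE − 1.645).

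| c | r | p | d (points) | SE | False non-inferiority |
|---|---|---|---|---|---|
| 2% | 80% | 0.8612 | 4.88 | 0.0205 | 5.6% |
| 4% | 60% | 0.8708 | 3.92 | 0.0202 | 13.4% |
| 6% | 60% | 0.8766 | 3.34 | 0.0201 | 20.6% |
| any | 86% (no gap) | 0.8600 | 5.00 | – | 5.0% |

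The shift equals c times the RFS gap between retained and withdrawn patients. At 1-2% withdrawn, a gap of 10-30 points moves the difference by only 0.1 to 0.6 points and the error to 5.5-8.9%.

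**Effect on FEV1.** Assume that retained segmentectomy patients show the 5% advantage the plan expects and that converted patients show none. The difference as randomised is then 5 × (1 − c): 4.9 at c = 2% and 4.7 at c = 6%. With these patients removed it reads 5.0. The Discussion supports the direction: it states that removing half the lobe or more costs about as much function as lobectomy.

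**Numbers of patients.** At c = 5%, 512 × 0.05 ≈ 26 patients would leave the segmentectomy arm, which is that arm's whole drop-out allowance.

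**The case against.** A reader might infer that the primary comparison is already fixed as successful segmentectomies against all lobectomies, and that every endpoint is biased toward segmentectomy. The documents do not support that, for these reasons:

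- **ITT is promised.** If every enrolled patient is followed and analysed as randomised, the bias does not arise in that analysis. This point stands, and it makes the bias conditional.
- **The withdrawal text is ambiguous.** Its opening sentence speaks of re-evaluation. This stands only in part, because the section heading, Table 1 and the Discussion ("the patients will be withdrawn from the study") all speak of withdrawal.
- **Follow-up is not expressly denied to withdrawn patients.** It is tempting to read the reference to qualified patients as shutting them out. Under Preoperative examinations, however, that word describes eligibility before surgery, and the 6-month spirometry covers every participant. The text neither stops nor guarantees their follow-up.
- **Item 3 applies to both arms**, as do the other withdrawal items. True; only the positive segmental margin and the half-lobe limit are specific to segmentectomy.
- **Frequency and prognosis are unknown.** Eligibility already requires that a satisfactory margin be achievable and that the planned resection be under half the lobe, which argues against assuming frequent conversion. Converted patients also end up with the comparator operation, so a worse RFS is plausible but not shown.
- **A condensed article may leave such handling to the full protocol.** Detail can be left out, but these rules are stated here and do not fit together.

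**Conclusion.** The concern holds as a conflict between stated rules. An event that the protocol orders or foresees in one arm is listed as a reason to leave the study, while ITT is promised for all enrolled patients.

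Whether the results are biased depends on what withdrawal means in practice. If it ends follow-up or removes patients from analysis, FEV1 and perioperative results would be expected to move toward segmentectomy, since a converted patient has a longer two-step operation and loses as much lung as after lobectomy. RFS moves too only if these patients fare worse. On the assumed rates, false non-inferiority rises from 5% to about 5.6-20.6%, and not at all without an RFS gap. The per-protocol set is also exposed, because a withdrawn patient has not completed the trial. A biased primary result is therefore a risk that the wording permits, not an established consequence.

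**What to change.** 1. Remove change of resection extent from the withdrawal list in the text and Table 1, and reconcile the half-lobe sentence in the Discussion with the ITT statement.
2. Classify converted or extended resections as protocol deviations or intercurrent events.
3. State that these patients are followed on the full Follow-up schedule and included in their randomised arm in the ITT analysis of RFS, OS, perioperative outcomes and FEV1.
4. Report conversions and other changes of extent by arm.
5. Record the planned segmentectomy for every patient before randomisation, and judge the under-half-lobe eligibility rule on that plan in both arms.

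When to convert is a clinical matter and is left as it is. The cost is a wording change and routine follow-up of a limited number of patients, with no extra enrolment. The segmentectomy result may look slightly less favourable.
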